## **OBJECTIVES**

### **2.1 Primary objective**

The primary objective of this project will be to investigate the effect of cane training and use on gait speed in individuals with PD.

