### **Sample calculation**

Twenty-six individuals will be included in this study. The sample size calculation was performed considering the clinically important difference in the primary outcome measure, gait speed. (Hass et al., 2014)Considering a significance level ( $\alpha$ ) of 5% and a

power of 0.80, an  $n=9$  was found for each group. Therefore, a sample size of 18 individuals. Assuming a sample loss of 30% of individuals throughout the study, a total sample of 26 individuals was determined, with 13 in each group.

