### **Data analysis**

The analysis will be performed by an independent researcher, blinded to the randomization of the groups, using intention-to-treat and per-protocol analysis. The normality of the data will be tested for all continuous numerical variables. Descriptive statistics will be used to characterize the sample and to investigate satisfaction with the use of the cane. The difference between the groups for the other outcome variables (gait speed, gait confidence, cadence, step length, functional mobility, freezing of gait) will be evaluated using repeated measures ANOVA, considering the measurements collected at the initial assessment, after training, and at follow-up. All statistical analyses will be performed using SPSS statistical software (SPSS Inc., Chicago, IL, United States). A significance level of  $\alpha=5\%$  will be established for all inferential analyses.

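### The repeated measures ANOVA includes the pre-randomisation visit as a response level, and the plan does not name the term, time point or estimate that answers the primary question

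*Combined protocol and SAP*

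**What the plan says.** The primary objective is to "investigate the effect of cane training and use on gait speed in individuals with PD". The inferential plan for this is one sentence under Data analysis. It covers gait speed and five further outcomes, and states that the comparison of the arms on each of them "will be evaluated using repeated measures ANOVA, considering the measurements collected at the initial assessment, after training, and at follow-up". A 5% level "will be established for all inferential analyses".

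Under Procedures, eligibility is checked at the initial assessment and included participants are allocated afterwards, so that visit comes before randomisation. Follow-up is one month after the post-training reassessment. The same section says that controls will be offered cane training after the study if the experimental group improves on the primary outcome relative to control.

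Under Sample calculation: "The sample size calculation was performed considering the clinically important difference in the primary outcome measure, gait speed", with "power of 0.80, an $n=9$ was found for each group", raised to 13 per group for 30% loss. The section gives no difference in m/s, SD, test or correlation between visits. Nowhere does the plan name an ANOVA term, a contrast, a primary time point, an effect estimate or a baseline covariate.

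**The concern.** A three-visit, two-group repeated measures ANOVA yields two tests that could be reported as the difference between the groups.

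- **Group main effect.** It compares the arms on the mean of all three visits. Baseline cannot carry a treatment effect, so including it dilutes the effect and brings chance baseline imbalance directly into the tested quantity.
- **Group-by-time interaction.** It asks whether the arms' profiles differ. Baseline is not averaged into the effect, but the test has 2 degrees of freedom and gives neither the direction nor the size of an effect, nor the visit at which it occurs.

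The two can disagree. With the term unnamed, the choice can be made after the data are seen, for the primary outcome and for five others. Direction matters here: the Introduction cites earlier studies in which a single-point cane slowed gait, and Procedures acts on an improvement, which is a signed result.

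**Working it through.** **Inputs from the documents.** Alpha 5%, power 0.80, 9 per group before loss, 30% loss, 13 per group enrolled, 1:1 allocation, three visits.

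**Assumed.** Two-sided test; normal data; equal SD at each visit; equal correlation ρ between visits, taken from 0.3 to 0.9.

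**The plan's own figure.** The loss step reproduces: 18/0.70 = 25.7, so 26; 9/0.70 = 12.9, so 13. The 9 per group cannot be derived forward, because no difference or SD is given. Back-solving for a two-sided t-test at one visit gives d = 1.407 SD: noncentrality 1.407 × √(9/2) = 2.98 on 16 df, power 80%. At 13 per group the same test has 93%. This d is used below.

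**Group main effect, sustained effect (0, d, d).**
- Difference in three-visit means: 2d/3 = 0.938.
- Variance of a three-visit mean: (1 + 2ρ)/3. At ρ = 0.7 this is 0.80, SD 0.894.
- Effective size 0.938/0.894 = 1.05; noncentrality 1.05 × √(9/2) = 2.23; power 55%.
- If the effect is gone by follow-up, the difference is d/3, and power at 9 per arm is 21%, 18%, 17% and 16% at ρ = 0.5, 0.7, 0.8 and 0.9.

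**Group-by-time interaction.** Noncentral F on 2 and 2(2n − 2) = 32 df, with λ = (n/2) × Σ(δₜ − mean δ)²/(1 − ρ).
- Sustained (0, d, d): the sum is (2/3)d² = 1.320. At ρ = 0.5, λ = 4.5 × 1.320/0.5 = 11.9; power 85%.
- Half lost by follow-up (0, d, d/2): the sum is d²/2 = 0.990. At ρ = 0.5, λ = 4.5 × 0.990/0.5 = 8.9; power 72%.
- Gone by follow-up (0, d, 0): the sum is again (2/3)d², so this test has the same power for a gain that is kept and one that vanishes.

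**ANCOVA at the post-training visit.** The residual variance is 1 − ρ². That closed form gives 83% and 90% at ρ = 0.3 and 0.5. Simulation, which also carries the cost of adjusting for chance baseline imbalance, gives 81% and about 88%. The table uses the simulated values. They do not depend on what happens at follow-up.

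| ρ | Main effect, sustained, n = 9 | Main effect, sustained, n = 13 | Interaction, sustained, n = 9 | Interaction, half lost, n = 9 | ANCOVA post-training, n = 9 |
|---|---|---|---|---|---|
| 0.3 | 72% | 88% | 70% | 57% | 81% |
| 0.5 | 63% | 80% | 85% | 72% | 88% |
| 0.7 | 55% | 73% | 97% | 92% | 96% |
| 0.8 | 52% | 69% | >99% | 99% | 99% |
| 0.9 | 49% | 66% | >99% | >99% | >99% |

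Simulation of the two ANOVA tests under a sustained effect (20,000 trials at each of ρ = 0.5, 0.7 and 0.8) agreed with the formulas to within about a point.

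**Type I error of the main effect.** With no effect it rejects in 5% of trials overall. The baseline gap has SD √(2/9) = 0.47, so it exceeds 0.5 SD in 29% of trials at 9 per arm. In those trials the main effect rejects about 15–18% of the time for ρ = 0.5 to 0.9.

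**The case against.** A reader might infer that the plan has chosen the diluted main effect, so that the stated 80% power does not hold. The documents do not support that. The sentence names no term, and including the initial visit fits a comparison of change, through the interaction, at least as well. On that reading a sustained effect keeps 85% power or more at ρ ≥ 0.5, close to post-training ANCOVA. This part of the objection stands: the defect is an unspecified test, not a demonstrably wrong one.

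A reader might also infer that chance imbalance inflates false positives. Overall type I error is 5%. The 15–18% is conditional on a large baseline gap, and an ordinary post-visit t-test rejects 9–16% in the same trials. This is no breach of the 5% level.

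The 9-per-arm figures assume the full 30% loss. With all 13 per arm, even the main effect has 66–80% at ρ 0.5 to 0.9. That also stands.

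Finally, one can say that ANCOVA over the interaction is only a preference about efficiency, and that the direction could be read off the group means. The first part is largely true for a sustained effect at ρ ≥ 0.5. It is not true when the effect wanes at low to moderate ρ. Reading direction off the means after an omnibus test is a step that the plan does not specify.

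**Conclusion.** The concern holds as a failure to specify. The plan makes the pre-randomisation visit one of three response levels and does not say which term, visit or estimate answers the primary question.

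- **If the main effect is used:** a sustained effect is cut to two thirds, with the loss of power shown in the table and overall type I error intact.
- **If the interaction is used:** there is no dilution and power is adequate for a sustained effect at ρ ≥ 0.5 (about 70% at ρ = 0.3). By itself it cannot show the improvement that Procedures acts on. With half the effect lost by follow-up it has 57% against 81% for ANCOVA at ρ = 0.3, and 72% against 88% at ρ = 0.5.

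All power figures rest on the back-solved d = 1.41 SD, equal SDs and an assumed common correlation; a different true effect or correlation would move them. The dilution to two thirds depends on none of these assumptions except that the effect is sustained. This is a should-fix: the remedy is simple, and one of the two plausible readings already gives a valid and reasonably powered test.

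**What to change.** Replace the repeated measures ANOVA sentence under Data analysis with wording such as:

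> For each outcome, the post-training and follow-up values are the responses and the initial-assessment value is a covariate, in a linear model for the two post-randomisation visits with group, visit, group-by-visit and baseline. The primary contrast is the baseline-adjusted difference between groups after training, with its 95% confidence interval. The adjusted difference at follow-up is secondary. The group main effect averaged over three visits including baseline will not be used.

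This gives a signed estimate at a named time, to which the condition in Procedures can refer. It also removes the choice between terms and takes baseline out of the averaged response.

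The cost is one degree of freedom for the covariate. The baseline values are already part of the planned analysis for these outcomes, and SPSS, the named software, fits the model. No further participants, visits or measurements are needed.

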**FINANCIAL BUDGET**

| Materials                | Unit cost | Total cost |
|---------------------------------|------------------|-------------------|
| 4 packs of A4 size office paper | R\$26.99         | R\$107.96         |
| 4 printer cartridges            | R\$90.00         | R\$360.00         |
| 13 Single-point canes           | R\$50.00         | R\$650.00         |
| Total: R\$ 1117.96              |                  |                   |

All expenses for this study will be covered by the researchers.

**TIMELINE**

| Period                                                         | 2023/2 | 2024/1 | 2024/2 | 2025/1 | 2025/2 | 2026/1 | 2026/2 |
|-----------------------------------------------------------------------|---------------|---------------|---------------|---------------|---------------|---------------|---------------|
| Bibliographic update                                                  |               |               |               |               |               |               |               |
| Fulfillment of credits                                                |               |               |               |               |               |               |               |
| Submission of the project to the Ethics Committee                     |               |               |               |               |               |               |               |
| Submission of the project to funding agencies.                        |               |               |               |               |               |               |               |
| Submission of the protocol for publication.                           |               |               |               |               |               |               |               |
| Recruitment period                                                    |               |               |               |               |               |               |               |
| Initial assessment                                                    |               |               |               |               |               |               |               |
| Revaluation                                                           |               |               |               |               |               |               |               |
| Follow-up                                                             |               |               |               |               |               |               |               |
| Partial and final statistical analysis and interpretation of results. |               |               |               |               |               |               |               |
| Thesis preparation and defense                                        |               |               |               |               |               |               |               |
| Forwarding for publication                                            |               |               |               |               |               |               |               |

Note: Recruitment and data collection will only begin after approval from the Ethics Committee. Therefore, adjustments to this timeline may be made depending on the date of the Ethics Committee approval.

## APPENDIX II - EVALUATION FORM

### RESEARCH PROJECT:

**EFFECT OF TRAINING AND USE OF A CANE ON THE MOBILITY OF INDIVIDUALS WITH PARKINSON'S DISEASE: A RANDOMIZED CLINICAL TRIAL**

**EVALUATION FORM (initial, re-evaluation or follow-up):** \_\_\_\_\_

**DATE:** \_\_\_\_\_ **TIME:** \_\_\_\_\_ **CODE:** \_\_\_\_\_

### 1. DEMOGRAPHIC DATA

- 1.1 Name: \_\_\_\_\_  
 1.2 Address: \_\_\_\_\_  
 1.2 Telephone: \_\_\_\_\_ Gender: ( ) Female ( ) Male  
 1.3 Date of Birth: \_\_\_\_\_ Age: \_\_\_\_\_  
 1.4 Marital status: \_\_\_\_\_ Lives with: \_\_\_\_\_  
 1.5 Education (years studied): \_\_\_\_\_ Training: \_\_\_\_\_  
 1.6 Occupation: \_\_\_\_\_  
 1.7 Companion (name and contact): \_\_\_\_\_

### 2 Clinical Data on PD

- 2.1 Time since onset of symptoms: \_\_\_\_\_ Diagnosis time: \_\_\_\_\_  
 2.2 Neurologist Diagnosis: ( ) YES ( ) NO  
 2.3 The more committed side: \_\_\_\_\_ Use of deep stimulation: ( ) YES ( ) NO  
 2.4 HY: \_\_\_\_\_ UPDRS-III: \_\_\_\_\_

### 3 GENERAL CLINICAL DATA

- 3.1 Dominant MS: \_\_\_\_\_ Dominant MI: \_\_\_\_\_  
 3.2 Visual impairment: ( ) No ( ) Yes Deficit Hearing: ( ) No ( ) Yes  
 3.3 Walks independently: ( ) No ( ) Yes  
 3.4 Number of associated diseases (description): \_\_\_\_\_  
 \_\_\_\_\_  
 3.5 Falls: How many times have you fallen in the last week? Month? In the last 6 months?  
 3.6 Are you currently doing any physical exercise? ( ) No ( ) Yes Which one? \_\_\_\_\_  
 How many times a week? \_\_\_\_\_. What is the duration (in minutes)? \_\_\_\_\_  
 3.7 Are you currently undergoing any rehabilitation treatment? (e.g., physiotherapy, occupational therapy, speech therapy, etc.) ( ) No ( ) Yes Which one? \_\_\_\_\_  
 How many times a week? \_\_\_\_\_ How long (in minutes): \_\_\_\_\_  
 3.8 Medications in use

| Medication | Dose | Time | Usage time |
|------------|------|------|------------|
|            |      |      |            |
|            |      |      |            |
|            |      |      |            |
|            |      |      |            |

Weight (kg): \_\_\_\_\_ Height (cm): \_\_\_\_\_  
 PA: \_\_\_\_\_ FC: \_\_\_\_\_ FR: \_\_\_\_\_ SatO2: \_\_\_\_\_

Able to use a single-tip cane: ( ) Yes ( ) No Reason: \_\_\_\_\_

### Mini Mental State Examination

| Time orientation                                                                                                                              |                                                                                                                                                                                                                                                                             | Points | Score |
|-----------------------------------------------------------------------------------------------------------------------------------------------|-----------------------------------------------------------------------------------------------------------------------------------------------------------------------------------------------------------------------------------------------------------------------------|--------|-------|
| What day is it today?                                                                                                                         |                                                                                                                                                                                                                                                                             | 1      |       |
| What month is it?                                                                                                                             |                                                                                                                                                                                                                                                                             | 1      |       |
| What year is it?                                                                                                                              |                                                                                                                                                                                                                                                                             | 1      |       |
| What day of the week is it?                                                                                                                   |                                                                                                                                                                                                                                                                             | 1      |       |
| What is the approximate time?                                                                                                                 | Consider a variation of one hour or less.                                                                                                                                                                                                                                   | 1      |       |
| Spatial orientation                                                                                                                           |                                                                                                                                                                                                                                                                             | Points | Score |
| Where are we located?                                                                                                                         | Consulting room, bedroom, living room - pointing to the floor                                                                                                                                                                                                               | 1      |       |
| What place is this?                                                                                                                           | Pointing around in a broader sense: hospital, nursing home, one's own home.                                                                                                                                                                                                 | 1      |       |
| What neighborhood are we in, or what is the name of a nearby street?                                                                          |                                                                                                                                                                                                                                                                             | 1      |       |
| Which city are we in?                                                                                                                         |                                                                                                                                                                                                                                                                             | 1      |       |
| What state are we in?                                                                                                                         |                                                                                                                                                                                                                                                                             | 1      |       |
| Immediate memory                                                                                                                              |                                                                                                                                                                                                                                                                             | Points | Score |
| I'm going to say three words and you will repeat them afterward: car, vase, brick.                                                            | Of 1 point to each word repeated correctly the first time, although they can be repeated. Up to three times for learning purposes, if there are mistakes.                                                                                                                   | 3      |       |
| CALCULATION                                                                                                                                   |                                                                                                                                                                                                                                                                             | Points | Score |
| Subtracting sevens sequentially:
How much is it?
100-7, 93-7, 86-7, 79-7, 72-7, 65                                                      | Award 1 point for each correct answer. If there is an error, correct it and proceed. Consider it correct if the examinee spontaneously self-corrects. (SEE*)                                                                                                                | 5      |       |
| Evocation of words                                                                                                                            |                                                                                                                                                                                                                                                                             | Points | Score |
| What words did you just say? repeat?                                                                                                          | Ask what words the subject had just used. Repeat - 1 point for each                                                                                                                                                                                                         | 3      |       |
| Appointment                                                                                                                                   |                                                                                                                                                                                                                                                                             | Points | Score |
| What object is this?                                                                                                                          | Ask the subject to name the objects shown (clock, pen) - 1 point for each.                                                                                                                                                                                                  | 2      |       |
| Repetition                                                                                                                                    |                                                                                                                                                                                                                                                                             | Points | Score |
| Listen carefully: I'm going to tell you a sentence.
And I want you to repeat after me:
"Neither here, nor there, nor anywhere."         | Consider only if the repetition is perfect (1 point)                                                                                                                                                                                                                        | 1      |       |
| Command                                                                                                                                       |                                                                                                                                                                                                                                                                             | Points | Score |
| "Take this paper with your right hand." (1 point), fold it in half (1 point) and place it on the floor (1 point)".                            | Total of 3 points. If the subject asks for help in the middle of the task, do not give hints.                                                                                                                                                                               | 3      |       |
| Reading                                                                                                                                       | Show the individual the written phrase 'CLOSE YOUR EYES' and ask them to do as instructed. Do not assist if you ask for help or if you only read. The phrase without carrying out the command.                                                                              | 1      |       |
| Phrase
Write a sentence.                                                                                                                   | Ask the individual to write a sentence. If you don't understand the meaning, help with: a sentence that has a beginning, middle, and end; Something that happened today; something you want to say. Grammatical or spelling errors are not considered for grading purposes. | 1      |       |
| Copy of the drawing:
Make a Copy this drawing as best as possible.                                                                         | Show the model and ask them to do their best. Only consider if there are 2 intersecting pentagons (10 angles) forming a figure with four sides or with two angles (1 point).                                                                                                | 1      |       |
| SCORING POINTS                                                                                                                         |                                                                                                                                                                                                                                                                             | 30     |       |
| 13 for illiterate people
18 for low/medium education (1 to 7 years of schooling)
26 for higher education (8 or more years of schooling) |                                                                                                                                                                                                                                                                             |        |       |

Spell the word WORLD backwards. one point for each letter in the position Correct - \*Note: Only the grade

*for the best performance will be considered.*

